### Intervention

Participants are allocated to standard care or enteral tube feeding in addition to standard care. Standard care consists of intravenous rehydration and, when considered necessary, laboratory monitoring, electrolyte and/or vitamin supplementation, antiemetic medication and dietetic advice. Type of rehydration regimen, medication and duration of hospitalisation is prescribed according to local protocol. In case of prolonged hospital admission or readmissions, tube feeding can be initiated at the decision of the attending physician.

When allocated to the intervention group, participants receive a nasogastric tube as soon as possible after randomisation, in addition to standard care. If the initial nasogastric tube is dislocated or poorly tolerated a nasoduodenal or nasojejunal insertion can also be considered. Tube feeding regimen and mix is prescribed according to local protocol. As soon as tube feeding is tolerated and participants have received safety instructions (e.g. recognising symptoms that need to be evaluated in hospital, because of potential tube blockage, dislocation or aspiration), discharge home with tube feeding is encouraged under the guidance of a hospital dietician. Energy intake per tube is continued at least until the patient is able to maintain an oral intake of 1000 cal per day for one week. According to the NICE guideline on nutrition, tube feeding in a home setting is considered to be safe [14].

### Data collection

At the day of randomisation, participants fill out a questionnaire. This questionnaire consists of validated NVP symptom and NVP specific quality of life measures (24-h Pregnancy Unique Quantification of Emesis and nausea score, PUQE-24; Hyperemesis Impact of Symptoms questionnaire, HIS; Nausea and Vomiting in Pregnancy Quality of Life questionnaire, NVPQoL) [7, 19–21], psychopathology (Hospital Anxiety and Depression Scale, HADS; Symptoms CheckList 90, SCL-90) [22–25] and general health related questions (Short Form 36, SF-36; EuroQol 5 Dimensions questionnaire,EQ5D) [26, 27].

Participants fill out additional questionnaires (NVPQoL, HIS, HADS) 1 and 3 weeks after randomisation and record a diary at weekly intervals (PUQE-24, weight, medication use, dietary intake) from randomisation until 20 weeks gestation. If dietary intake has normalised from 15 weeks gestation onwards, this is no longer recorded. Six weeks postpartum (HADS, SF-36, EQ5D) and 12 months postpartum a final questionnaire is filled out (HADS, SF-36, EQ5D, SCL-90). See Table 1.

**Table 1 Tab1:** Time line MOTHER trial

	T0	T1	T2	T3	T4	T5	T6	T7
	*Randomisation*	*+1 week*	*+ 2 weeks*	*+ 3 weeks*	*+ 4 weeks until GA 20 weeks*	*Birth*	*6 weeks post-partum*	*12 months post-partum*
Diary								
PUQE	X	X	X	X	X			
Current weight	X	X	X	X	X			
Medication use	X	X	X	X	X			
Dietary intake	X	X	X	X	X^a^			
Questionnaires								
General health	X							
NVPQoL	X	X		X				
HIS	X	X		X				
HADS	X	X		X			X	X
SF-36	X						X	X
EQ5D		X					X	X
SCL-90	X							X
Biobank material								
Maternal blood	X							
Cord blood						X		
Placental biopsies						X		

*PUQE* pregnancy unique quantification of emesis and nausea score, *NVPQoL* nausea and vomiting in pregnancy quality of life questionnaire, *HIS* hyperemesis impact of symptoms questionnaire, *HADS* hospital anxiety and depression scale, *SF-36* short form 36, *EQ5D* euroQol 5 dimensions questionnaire, *SCL-90* symptoms checklist 90

^a^If dietary intake has normalised from GA 15 weeks onwards, this will be no longer recorded

To evaluate potential HG and birth weight predictors, detailed information on obstetric and medical history, anthropometrics (before and during pregnancy), antiemetic medication use, given treatment(s) (including intravenous and/or tube feeding regimen and tube location), laboratory results, treatment and pregnancy complications and birth outcomes are collected using a standardised Case Report Form (CRF; see Additional file 1). Research staff obtains the information needed based on medical and dietician records. Maternal demographics (ethnicity, education level, marital status), mode of conception and onset of nausea and vomiting symptoms are enquired via the questionnaire.

All participants in this trial are asked for informed consent of storage of maternal blood (taken with routine laboratory analysis during hospital admission for HG), cord blood and placental biopsies (taken at birth) in an obstetrical biobank (the Preeclampsia and Non-preeclampsia Database, Academic Medical Centre Amsterdam, the Netherlands). The addition of these samples will enable molecular studies in HG aetiology and consequences. Furthermore, cord blood will be used for the assessment of plasma lipids (cholesterol, HDL, LDL, triglycerides, Apolipoprotein A and B), glucose, leptin and thyroid function (TSH, fT4).

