## Methods/Design

### Participants/ eligibility criteria

Patients ≥ 18 years of age are eligible if they have been admitted to hospital because of HG (first admission or readmission) at a gestational age between 5 + 0 and 19 + 6 weeks. Patients with singleton or multiple pregnancies are eligible. A diagnosis of HG is made if excessive nausea or vomiting necessitates hospital admission, in the absence of any other obvious cause such as drug induced vomiting or infection.

Exclusion criteria are mola hydatidosa pregnancy, non-vital pregnancy, acute infection causing vomiting (e.g. appendicitis, pyelonephritis), contraindication for enteral tube feeding (e.g. oesophageal varices, allergies to enteral tube mix compounds) or HIV infection.

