### Secondary outcome measures

Secondary outcomes will be the validated PUQE-24 score one week after randomisation, maternal weight gain, dietary intake, HIS, NVPQoL, EQ5D, SF-36, HADS and SCL-90 scores, urinary ketones, duration of hospital stay and number of readmissions. Furthermore, gestational age at birth, preterm birth rate, small for gestational age (SGA; <10^th^ percentile) placental weight, umbilical cord plasma lipids, neonatal hypoglycaemia, hyperbilirubinaemia and congenital anomalies will be evaluated. Lastly, we will evaluate maternal side effects of tube feeding and intravenous rehydration and reasons for discontinuation of the allocated treatment.

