### Data analysis

Data will be analysed according to the intention to treat principle. Difference in birth weight will be assessed using parametric testing. PUQE-24 score will be analysed using multivariate regression and repeated measurements ANOVA or mixed models, as will be quality of life assessments. Other secondary outcomes will be addressed in a similar manner. For non-normally distributed variables non-parametric equivalents will be used. To evaluate the potential of each of the strategies, we will also perform a per protocol analysis, taking into account only those women that were treated according to protocol.

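### From 15 weeks' gestation, dietary intake stops being recorded once it has 'normalised' (an undefined term), so late diaries over-represent unrecovered women and one permitted analysis would distort the arm difference

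*Protocol article*

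**What the plan says.** All places are in the protocol article.

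- **Data collection.** Women keep a weekly diary "from randomisation until 20 weeks gestation", covering PUQE-24, weight, medication and dietary intake. For dietary intake alone there is a stopping rule: "If dietary intake has normalised from 15 weeks gestation onwards, this is no longer recorded".
- **Table 1, footnote a.** The rule is repeated: "If dietary intake has normalised from GA 15 weeks onwards, this will be no longer recorded". The footnote mark sits only on the dietary-intake cell of the T4 column (4 weeks after randomisation until 20 weeks' gestation). The T0 to T3 cells carry a plain X. PUQE, weight and medication have no such footnote.
- **Secondary outcome measures.** Dietary intake is listed among the secondary outcomes ("maternal weight gain, dietary intake, HIS, NVPQoL" and others), with no time point of its own.
- **Participants/eligibility criteria.** Women may enter "at a gestational age between 5 + 0 and 19 + 6 weeks".
- **Data analysis.** "PUQE-24 score will be analysed using multivariate regression and repeated measurements ANOVA or mixed models". For the rest: "Other secondary outcomes will be addressed in a similar manner". The analysis is by intention to treat.

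The article does not say what intake counts as normalised, who decides, or whether recording resumes after a relapse.

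**The concern.** A repeated measurement that stops because of its own value leaves a selected group behind. From 15 weeks, women eating normally can leave the intake record while women eating poorly stay in it. If tube feeding speeds recovery, as the trial hypothesises, more women leave from the tube-feeding arm. The late diaries then compare the unrecovered part of one randomised group with the unrecovered part of the other, which is no longer an intention-to-treat comparison.

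The analysis text leaves two routes open. Classical repeated-measures ANOVA needs a complete series from each woman, so it would discard those who stopped because they had recovered. A mixed model keeps their earlier diaries. The two can give quite different answers here.

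Intake is the most direct measure of whether a nutritional intervention does what it is meant to do. A distorted result would weaken the explanation of whatever is found for birth weight and symptoms. The primary outcome itself is not touched.

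**Working it through.** The article gives no figure for dietary intake, so there is none to reproduce. The check has two parts: what the rule covers, and how much it could matter.

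**1. What the rule covers.** Before 15 weeks every woman records intake, recovered or not. The rule can act only from 15 weeks to the end of the diary at 20 weeks. Because entry is allowed up to 19+6, a woman randomised after 15 weeks has her whole diary inside that window. Text and table differ slightly. For a woman randomised after 12 weeks, the visit 3 weeks later falls after 15 weeks; the text would let recording stop there, while Table 1 marks it as recorded without qualification.

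**2. Simulation.** Every input below is an assumption, since the article supplies none. Intake in kcal/day for woman i in week w (9 to 20):

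Y = 900 + 80 × (w − 9) + b + δ(w) × T + e

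Here b has SD 400 (between women), e has SD 300 (within woman), T = 1 for tube feeding, and δ applies from week 10. There are 20,000 women, allocated 1:1. Recording stops after the first value at or above a threshold in week 15 or later, and that value is itself recorded.

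Constant true effect, difference among recorded diaries in weeks 16 to 20. Share lost = 1 − observed/true:

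| True effect | Threshold | Recorded-only difference | Share lost | Still recording at week 20, control v tube |
|---|---|---|---|---|
| 200 | 1500 | 103 | 48.5% | 18% v 9% |
| 200 | 1800 | 107 | 46.5% | 40% v 24% |
| 200 | 2000 | 127 | 36.5% | 57% v 40% |
| 400 | 1500 | 198 | 50.5% | 18% v 3% |
| 400 | 1800 | 215 | 46.3% | 40% v 12% |
| 400 | 2000 | 229 | 42.8% | 57% v 24% |

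**Complete series.** With no other missing data, the women with a complete series are exactly those still recording at week 20. The week-20 contrast available to a complete-series ANOVA is therefore the recorded-only one: 101, 68 and 98 for a true 200, and 106, 158 and 182 for a true 400 (thresholds in the same order).

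**Fading effect.** With δ(w) = d × (20 − w)/11, the true week-20 difference is 0. The recorded-only week-20 difference was −27, −32 and −28 for d = 200, and −53, −57 and −37 for d = 400. That is a small spurious reversal.

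**Up to week 15.** Recording was complete through week 15 in every scenario, so those comparisons are unaffected.

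**Mixed model.** A random-intercept model was fitted to all recorded weeks after week 9 (3,000 women, constant effect 200). It gave a late difference of 216 where the full data of the same draw gave 217 (threshold 1500), and 192 where they gave 200 (threshold 1800). Recorded-only differences in those draws were 97 and 105.

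**The case against.** The strongest reply is that the article also names a mixed model, and that model deals with the problem. When stopping depends only on a value already recorded, the gaps are missing at random given the diary, and the simulation confirms that nearly the whole difference comes back. Nowhere does the article plan a comparison of raw weekly means after 15 weeks. Time point, model choice and handling of gaps are things an article may leave to the full protocol or analysis plan. Early diaries are complete, weight and PUQE run on to 20 weeks, and reducing diary burden is a reasonable aim.

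Much of this stands. A reader might infer that the rule spoils the intake outcome as a whole, that half of any effect is bound to be lost, or that the bias always runs towards no difference. The documents support none of these. The rule begins only at 15 weeks. The losses shown come from assumed inputs and a raw comparison. A fading effect can produce a reversal instead of attenuation. Nor does the article commit to ANOVA. The missing time point is not counted against it.

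Two things survive. First, an analysis plan cannot recover intake that the design chose not to collect, and one of the two methods the article permits gives a wrong answer on such data. Second, the mixed model is safe only if stopping follows recorded intake. With 'normalised' undefined in an open-label trial, the judgement could rest on unrecorded grounds or differ by arm. For example, the article does not say whether oral or total intake counts while a tube is in place. If the week that triggers stopping is itself left blank, stopping also depends on a value nobody recorded.

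**Conclusion.** The point holds in a limited form. From 15 to 20 weeks the intake record is selected on the outcome. If tube feeding improves intake, a comparison of recorded late diaries, or an ANOVA on complete series, is likely to understate or distort the arm difference. Data before 15 weeks are sound, except that women who enter after 15 weeks have none.

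The size and direction cannot be derived from the document. They depend on whether there is an effect on intake, whether it lasts, what counts as normalised, whether late diaries enter the comparison, and which model is used. The simulated losses show only that the distortion could be material under a raw comparison. The near-complete recovery by the mixed model rests on stopping that depends only on recorded intake and on a model that matches how the data were generated.

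This concerns one secondary outcome among many, but the change is cheap and worth making.

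**What to change.** **Data collection.** Define 'normalised' in advance, in the same terms for both arms, and state who applies the definition. Replace the stopped record with one weekly tick box on the diary that already runs to 20 weeks: intake still normal, yes or no, with full recording resumed if no. Make the text and the Table 1 footnote agree on when the rule can first apply.

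**Analysis.** For dietary intake, drop the repeated-measures ANOVA option. Use a likelihood-based mixed model on all recorded diaries of all randomised women, with time to normalised intake as a supporting analysis. Do not compare raw means among women still recording after 15 weeks. Do not solve the problem by cutting the quantitative analysis off at 15 weeks either: entry is allowed up to 19+6, so that would drop late entrants and break the intention-to-treat comparison.

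**Cost.** One extra diary item and a few lines of text. For diaries already stopped the intake cannot be recovered, and the analysis must assume that stopping depended only on recorded intake; the report should say so.

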## Outcome measures

### Primary outcome measure

The primary outcome will be neonatal birth weight.

### Secondary outcome measures

Secondary outcomes will be the validated PUQE-24 score one week after randomisation, maternal weight gain, dietary intake, HIS, NVPQoL, EQ5D, SF-36, HADS and SCL-90 scores, urinary ketones, duration of hospital stay and number of readmissions. Furthermore, gestational age at birth, preterm birth rate, small for gestational age (SGA; <10^th^ percentile) placental weight, umbilical cord plasma lipids, neonatal hypoglycaemia, hyperbilirubinaemia and congenital anomalies will be evaluated. Lastly, we will evaluate maternal side effects of tube feeding and intravenous rehydration and reasons for discontinuation of the allocated treatment.

### Follow-up of infants

A plan for long-term follow up of children is in preparation, because little is known about the long term health effects of babies born to mothers whose pregnancies were complicated by HG and we have reason to hypothesise that maternal malnutrition during early pregnancy has long term effects on the offspring’s cardiometabolic health [4]. Funding for follow-up has not yet been obtained.

## Statistical issues

### Sample size

The sample size is based on a difference in mean birth weight of 200 g (SD 400 g) between the intervention group and the control group, which we consider clinically relevant. With a beta of 0.2 and alpha of 0.05 and a possible 10 % loss to follow up, we need to randomise 120 participants (60 per arm). This sample size is also large enough to detect a two point reduction in PUQE-24 score 1 week after randomisation (maximum 15 points, SD 3 points) and differences in quality of life, psychopathology and general health questionnaires ≥ 10 %.

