**Fig. 1 Fig1:**
[figure not shown]
CONSORT 2010 flow diagram MOTHER trial

Randomisation is performed by a web based computerised program using permuted-block randomisation. Randomisation is allocated in a 1:1 ratio for standard care or enteral tube feeding in addition to standard care, with a block size of four. Stratification according to centre is applied.

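### The 120 women planned give about 73% power, not 80%, for the stated 200 g birth-weight difference if the test is two-sided; sidedness is not stated

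*Protocol article*

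**What the plan says.** The Sample size section of the protocol article gives a full set of inputs for the primary outcome. The target is a "difference in mean birth weight of 200 g (SD 400 g" in each group. The error rates are set by "With a beta of 0.2 and alpha of 0.05", and the number allows for "a possible 10 % loss to follow up". From these it concludes "we need to randomise 120 participants (60 per arm". Elsewhere the article fixes equal allocation ("Randomisation is allocated in a 1:1 ratio") and, under Data analysis, names the primary comparison: "Difference in birth weight will be assessed using parametric testing". It does not say whether alpha is one-sided or two-sided. For birth weight it states no covariate adjustment or other reduction of variance. The same section adds that the sample is large enough for a two-point change in PUQE-24 at one week (SD 3), and for questionnaire differences of 10% or more.

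**The concern.** A difference of half a standard deviation is a familiar case: about 64 analysed per arm for 80% power at two-sided 0.05. A plan that randomises 60 per arm, and says this already includes 10% loss, is below that before any loss occurs. If the usual two-sided test is meant, the trial claims a power for its primary outcome that it does not have. A true effect of exactly the size the authors consider worth detecting would then be missed more often than stated, and a null result would be read against the wrong figure. If a one-sided test is meant, an undeclared choice decides whether the sample size holds.

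**Working it through.** **Inputs** (protocol article, Sample size, unless noted): difference 200 g; SD 400 g, so d = 200/400 = 0.5; beta 0.2; alpha 0.05; loss 10%; 60 per arm randomised, so 60 × 0.9 = 54 per arm analysed; 1:1 allocation (paragraph under Fig. 1); parametric two-group comparison (Data analysis). Sidedness is not given, so both readings are tried.

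**Step 1. Try to reproduce 120.** Analysed per arm, normal approximation: n = 2 × (z_alpha + z_beta)² × (SD/difference)².

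- Two-sided: 2 × (1.960 + 0.842)² × 4 = 62.8, so 63. The t-based value is 64.
- One-sided: 2 × (1.645 + 0.842)² × 4 = 49.5, so 50. The t-based value is 51.

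Dividing by 0.9 for loss:

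| Reading | Analysed per arm | Randomised per arm | Total | Stated |
|---|---|---|---|---|
| Two-sided, 10% loss | 63–64 | 70–72 | 140–144 | 120 |
| Two-sided, loss ignored | 63–64 | 63–64 | 126–128 | 120 |
| One-sided, 10% loss | 50–51 | 56–57 | 112–114 | 120 |

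Multiplying by 1.1 instead of dividing by 0.9 gives 70 to 71 per arm two-sided, so the method of inflation does not explain the gap. No reading yields exactly 120. The one-sided reading is the only one that 120 covers.

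**Step 2. Power of the plan as stated.** Normal approximation: power = Φ(d × √(n/2) − z_alpha). The t column is from the noncentral t distribution.

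| Analysed per arm | Test | Normal | t |
|---|---|---|---|
| 54 | two-sided | Φ(2.598 − 1.960) = 73.8% | 73.1% |
| 60 (no loss) | two-sided | Φ(2.739 − 1.960) = 78.2% | 77.5% |
| 54 | one-sided | Φ(2.598 − 1.645) = 83.0% | 82.6% |

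The two-sided type II error at 54 per arm is 100 − 73.1 = 26.9%.

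**Step 3. What 54 per arm can detect with 80% power, two-sided.** Normal: 400 × (1.960 + 0.842) × √(2/54) = 216 g. By the t test the detectable standardised difference is 0.544, and 0.544 × 400 = 218 g. Equivalently, 200 g would be detectable only if the SD were about 371 g (normal) instead of 400 g.

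**Step 4. The PUQE-24 statement.** 2 × (1.960 + 0.842)² × (3/2)² = 35.3, so 36 per arm. At 54 per arm, power = Φ((2/3) × √27 − 1.960) = Φ(3.464 − 1.960) = 93%. This statement is sound.

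**The case against.** The best reply is that the article never says the test is two-sided, and the hypothesis at the end of its Background is directional: tube feeding is expected to do better. On a one-sided 0.05 test, 56 to 57 per arm are needed after loss, and 60 per arm could be that figure rounded up. This stands as far as it goes, and it is why the shortfall is stated here as conditional on two-sided testing. It does not rescue the text. A directional hypothesis does not declare a one-sided test, the sample-size and analysis sections both speak simply of a difference, and 112 to 114 is not 120.

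It can also be said that the gap is modest: 218 g against 200 g, with no bias in the estimate and no inflation of the type I error. That is true, and it is why restating the figure is enough.

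Two stronger inferences are tempting but not supported. First, a reader might infer that the claim about "differences in quality of life, psychopathology and general health questionnaires" also fails. The article does not say what the 10% is a percentage of. The PUQE-24 SD cannot be carried over to other instruments. A detectable difference based on an unadjusted t test would also ignore the regression, repeated-measures or mixed models planned for quality of life. Standard deviations for secondary instruments may reasonably be left to the full protocol. Second, a reader might infer that covariate adjustment of birth weight restores 80% power. The article plans no such adjustment and gives no figure for the variance it would explain.

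**Conclusion.** The primary-outcome power is wrong as written under the conventional two-sided test: about 73% instead of 80%, a deficit of about 7 percentage points, or 20 to 24 women short of the 140 to 144 required. The result rests on the article's own difference, SD, loss and allocation, on an unadjusted comparison of two means, and on alpha 0.05 being two-sided. Only the last is an assumption about something the text leaves open, and the one reading that avoids the shortfall is not declared. This is an inconsistency between printed inputs and a printed result, so it is not explained by the article being a condensed version of a fuller protocol. The finding is confined to birth weight.

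**What to change.** In the Sample size section, state that alpha is two-sided and replace the power sentence with wording such as: 120 women randomised, of whom 108 are expected to be analysed after 10% loss, give about 73% power for a 200 g difference in mean birth weight, or 80% power for a difference of about 218 g (SD 400 g). Leave the PUQE-24 sentence as it is. This point requires no change to the questionnaire sentence. The cost is a wording change and a less favourable stated power. No additional women are needed.
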